#### Development of Prediction Model and Sample Size Calculation

An exploratory multimodality model will be created to predict the primary endpoint (ablation success). Ideally, to develop a reliable prediction model all variables of interest that will be studied in the model should be defined prior to the data collection. However, this study includes several relatively new techniques, which each provide a multitude of possible variables of interest for which the predictive value has not been established. Defining variables to be included in the model up-front could limit its eventual predictive value, as the predefined variables might not prove to be the most discriminative variables. Therefore, an exploratory analysis of variables in the following categories will be performed first (Figure 1): (1) clinical risk factors, (2) pre-procedural AF patterns, (3) anatomical characteristics, (4) electrophysiological characteristics, (5) circulating biomarkers, and (6) genetic background. For subcategory 1–5 the three variables with the strongest correlation to ablation success are selected and presented to the model. For subcategory 6 the two strongest predictors are used. The ablation technique that is chosen is used as a separate predictor. This approach leads to a total of 18 variables used to develop the multimodality model. To ensure sufficient power to explore these 18 variables, a total of 180 events is required to conform to the rule-of-thumb to aim for 10 events per variable. When assuming an event rate of 32% (68% successful AF ablations) (4, 5), inclusion of 563 patients is required to achieve sufficient events. Accounting for a lost-to-follow-up rate of 15%, the aim is to include 650 patients scheduled for first catheter ablation.

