Variables with possible interrelation (e.g., left atrial volume index or AF type with chosen ablation technique) will be tested for interaction and, if present, interaction terms will be included in the model. The model will be developed using logistic regression by forward selection with the use of the Akaike Information Criterion (AIC) as stopping rule. The discriminative performance of the model is evaluated by calculating the area under the receiver operator characteristic (AUROC) curve (C-statistic) and by comparisons of observed groups of different predictive frequencies. To assess the potential confounding effect of the ablation strategy that was chosen, performance analyses will be done for the entire cohort and separately for patients treated with different ablation strategies for sensitivity purposes.

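### Model performance is assessed in the same cohort that screened, selected and fitted the model, with no internal validation described, so the C-statistic is an apparent one and biased upward

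*Protocol article*

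**What the plan says.** All of this is in the Protocol article, section Development of Prediction Model and Sample Size Calculation.

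- **Purpose.** "An exploratory multimodality model will be created to predict the primary endpoint (ablation success").
- **Candidate pool.** The new techniques are described as ones "which each provide a multitude of possible variables of interest for which the predictive value has not been established". No count is given. The article states that "an exploratory analysis of variables in the following categories will be performed first".
- **Screening by outcome.** The rule for the first five domains is: "For subcategory 1–5 the three variables with the strongest correlation to ablation success are selected and presented to the model". Genetics gets a smaller quota under the same kind of ranking: "For subcategory 6 the two strongest predictors are used". One further variable bypasses the ranking altogether: "The ablation technique that is chosen is used as a separate predictor". That makes 18 variables, and the sample size is set at 10 events for each of them.
- **Model building.** Possibly related variables are tested for interaction, and terms are added where one is found. The logistic model is then built by forward selection with AIC as the stopping rule.
- **Evaluation.** "The discriminative performance of the model is evaluated by calculating the area under the receiver operator characteristic (AUROC) curve (C-statistic"). The same sentence adds a second measure, observed outcomes compared across groups of predicted risk. To examine confounding by ablation strategy, "performance analyses will be done for the entire cohort and separately for patients treated with different ablation strategies".

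The article mentions no hold-out set, resampling, shrinkage or optimism correction. Overfitting is not among its five listed limitations.

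**The concern.** The outcome data are used at least three times before performance is measured: to rank candidates within domains, to decide on interaction terms, and to choose and fit the final model. An AUROC computed in those same patients describes how well the search fitted this sample. It does not estimate how well the model would separate successes from recurrences in the next patients.

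The other two checks do not repair this. The observed-by-predicted groups are formed from the same fitted probabilities in the same patients. The analyses by ablation strategy evaluate the model in subsets of the development cohort. The rule of 10 events per variable does not help either, because it counts only the 18 variables left after screening and ignores the candidates discarded on the strength of the outcome.

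What is at stake is the use the article foresees. Its abstract, Introduction, Discussion and Conclusion all suggest that the results may inform patient selection and tailoring of treatment. An inflated C-statistic would overstate the support for that use.

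**Working it through.** **1. The plan's own figures.** Variables: 5 × 3 + 2 + 1 = 18. Events: 18 × 10 = 180. Patients: 180 / 0.32 = 562.5, so 563, as stated. Allowing for 15% loss, 563 / 0.85 = 662.4 (663), or 563 × 1.15 = 647.4 (648). The stated 650 lies close to both. With 650 enrolled, 650 × 0.85 = 552.5 patients and 552.5 × 0.32 = 176.8 events, or 176.8 / 18 = 9.8 events per variable. The arithmetic broadly holds, but only for the variables that survive screening.

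**2. What the rule leaves out.** With m candidates in each of six domains plus ablation technique, the search covers 6m + 1 variables. Events per candidate are 180 / (6m + 1).

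**3. Simulation of the described procedure with no true predictor.** From the article: 563 patients, 32% events, top 3 (top 2 for genetics) by absolute correlation with outcome, technique always offered, forward AIC. Assumed: m, independent standard-normal candidates, technique as a single term, no interaction terms, no missing data. Each row is 100 runs, and the comparison is 5,000 new patients per run.

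| m per domain | candidates 6m + 1 | events per candidate | mean apparent AUROC | AUROC in new patients | runs with apparent AUROC ≥ 0.70 |
|---|---|---|---|---|---|
| 3 | 19 | 9.5 | 0.582 | 0.500 | 0% |
| 5 | 31 | 5.8 | 0.604 | 0.499 | 0% |
| 10 | 61 | 3.0 | 0.647 | 0.498 | 2% |
| 20 | 121 | 1.5 | 0.685 | 0.501 | 21% |
| 50 | 301 | 0.6 | 0.724 | 0.500 | 96% |

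The optimism (apparent minus new-patient value) runs from 0.08 to 0.22.

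A separate run with 553 patients gave 0.57, 0.66 and 0.69 for m = 3, 10 and 20. With a correlation of 0.5 between candidates in the same domain, it gave 0.57, 0.62 and 0.64.

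**4. With weak real signal** (assumed: one true predictor per domain, log-odds 0.2 per standard deviation, 60 runs each). Apparent AUROC was 0.66, 0.69 and 0.72 for m = 3, 10 and 20, against 0.60, 0.58 and 0.57 in new patients. The bias does not depend on the all-null setting.

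**5. Which correction works** (25 runs each, 20 bootstrap samples).

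| Setting | Apparent | 10-fold CV, all steps | Bootstrap, all steps | Bootstrap, final refit only |
|---|---|---|---|---|
| Null, m = 10 | 0.647 | 0.500 | 0.540 | 0.616 |
| Null, m = 20 | 0.683 | 0.490 | 0.557 | 0.645 |
| Weak signal, m = 20 | 0.713 | 0.557 | 0.600 | 0.679 |

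Under the null, the whole-pipeline bootstrap leaves 0.040 / 0.147 = 27% of the bias at m = 10 and 0.057 / 0.183 = 31% at m = 20. Refitting only the final model leaves 0.116 / 0.147 = 79% and 0.145 / 0.183 = 79%. Cross-validation of every step returns about 0.50. In the weak-signal row it gives 0.56, against 0.57 in new patients.

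**The case against.** **The document is a condensed article.** The full protocol or an analysis plan may specify validation, so its absence is known only of this text. That stands as a caution. But the article does more than stay silent: it fixes the screening counts, the selection method, the stopping rule, the performance measures and the patients in whom performance is assessed. Followed as written, those instructions produce an apparent C-statistic.

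**The model is labelled exploratory, and clinical use is worded conditionally.** This is true, and the article openly says that predefined variables would be the ideal. It softens the consequence but does not make the statistic unbiased.

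**The size rests on assumed inputs.** This is also fair. Measurements within a domain are likely to be correlated, which lowers the optimism. The Introduction cites established predictors, so a world in which nothing predicts is a yardstick and not an expectation.

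Two stronger readings are tempting, and the document does not support them. A reader might infer that AUROC is the only criterion, but the same sentence adds the comparison of observed groups. A reader might also infer that the model is bound to look useful even if nothing predicts. That depends on a candidate count the article does not give: with 3 per domain the null AUROC is about 0.58, which would impress nobody.

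**Conclusion.** The point holds as a statement about direction. The described evaluation uses the development cohort after an outcome-driven search, so the C-statistic is optimistic at every candidate count tried. The size is conditional. Under no true signal, the mean apparent AUROC ranges from about 0.57–0.58 (3 per domain) to 0.72 (50 per domain) with independent candidates, and is about 0.62–0.64 for 10 to 20 per domain at correlation 0.5, against a true 0.50. With weak real signal the excess was 0.06 to 0.15 (0.659 − 0.600 = 0.059 at m = 3; 0.717 − 0.569 = 0.148 at m = 20).

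These figures rest on assumed candidate counts, normal candidates, technique as one term, no interaction terms and complete data. Adding interaction terms chosen by testing would raise the optimism. The conclusion applies to the article as published; validation specified in a fuller document would answer it, provided it repeats the screening step.

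**What to change.** In the section on development of the prediction model:

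- Make the reported performance figure the one from repeated 10-fold cross-validation in which every step is re-run within each fold: imputation, domain screening, interaction testing and forward AIC selection.
- Report cross-validated AUROC and calibration.
- Label any AUROC computed in the development patients as apparent. Keep the analyses by ablation strategy for their stated purpose, and do not present them as validation.
- State how many candidates are screened in each domain, so that a reader can judge the extent of the search.

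A bootstrap that refits only the final model is not enough. A whole-pipeline optimism bootstrap is better but left 0.54 to 0.56 under the null, so cross-validation is preferred. Developing in one centre and testing in the other is not required to remove this bias, and would leave each part short of the plan's own 10 events per variable.

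**Cost.** No new patients or measurements. It takes computing time, analysis code that may go beyond the standard menus of the named SPSS package, and acceptance of a lower reported AUROC.

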### Atrial Fibrillation Ablation

AF ablation comprises pulmonary vein isolation (PVI) with or without additional lesions. The type of ablation that is performed is determined in a multidisciplinary team meeting and depends on the patient’s preference and characteristics. The choice of ablation strategy is not influenced by study participation. In the participating centers, first ablations for paroxysmal AF and for persistent AF with normal to modestly dilated atria or in elderly patients are usually performed by cryoablation (Figure 2). First ablations for persistent AF with advanced atrial dilation or with concomitant atrial flutter or atrial tachycardia are mostly performed by wide atrial circumferential ablation (WACA) using radiofrequency applications, if needed complemented with cavo-tricuspid isthmus ablation (in case of typical atrial flutters). Patients with longstanding persistent AF (> 1 year) are usually treated with thoracoscopic or hybrid AF ablation. Patients with recurrent AF undergoing a second (redo) procedure are mainly treated with radiofrequency ablation or thoracoscopic/hybrid AF ablation, whereas for third or further procedures hybrid procedures are recommended, if patients are suitable candidates and no earlier hybrid treatment was performed. Patients with an indication for cardiac surgery and known AF are discussed in an arrhythmia team and considered for concomitant epicardial AF ablation. Treating physicians may choose to deviate from these recommendations depending on specific patient characteristics and patient preference. All patients planned to undergo an endocardial procedure are treated with oral anticoagulants around the ablation (3). In addition, a transesophageal echocardiogram is performed prior to all endocardial procedures to exclude intracardiac thrombi.

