### Limitations

The ISOLATION study and ISOLATION “light” registry have several limitations. First, the type of AF ablation that is performed is not standardized but is decided upon by a patients’ treating physician. Success rates of different strategies vary and this may impact the rate in which the primary endpoint occurs. Second, monitoring for recurrences of atrial arrhythmia is performed intermittently using ECGs, Holter recordings, and PPG-based monitoring, but lack of continuous rhythm monitoring may lead to an underestimation of the number of endpoints (18). Third, only AF patients scheduled for AF ablation are included. Results found in this cohort may not be generalizable to the entire AF population. Fourth, not all patients undergoing AF ablation will agree to study participation. Although the integration with the ISOLATION “light” registry helps to include nearly all patients undergoing AF ablation, the specific study procedures are only conducted for participants in the main ISOLATION study. Fifth, the study reflects a large, real-world cohort of AF ablation patients. Due to the world-wide COVID-19 pandemic and to incident logistical reasons, protocol deviations may occur (e.g., a longer than desirable waiting time for ablation or out-of-window follow-up visits).

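### Model performance overall and within ablation strategies cannot show whether strategy confounds the predictors, because it cannot be separated from case mix

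*Protocol article*

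**What the plan says.** All references are to the protocol article.

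- **Development of Prediction Model and Sample Size Calculation**, on confounding: "To assess the potential confounding effect of the ablation strategy that was chosen, performance analyses will be done for the entire cohort and separately" by strategy, the latter as a sensitivity analysis.
- The same section names two performance measures: the C-statistic, and a second one obtained "by comparisons of observed groups of different predictive frequencies". The second is loosely worded; it is most naturally read as observed outcome by group of predicted risk.
- The same section also handles strategy inside the model: "The ablation technique that is chosen is used as a separate predictor". Variables that may be related to the chosen technique, with left atrial volume index and AF type as the examples, "will be tested for interaction and, if present, interaction terms will be included in the model". Selection is forward, stopped by AIC. Technique is not stated to be exempt from selection.
- **Atrial Fibrillation Ablation**: "The type of ablation that is performed is determined in a multidisciplinary team meeting and depends on the patient", meaning the patient's preference and characteristics. The usual choices follow AF type and duration, atrial dilation, age, concomitant flutter or tachycardia, and previous ablation.
- **Limitations** gives non-standardised strategy as the first limitation: "Success rates of different strategies vary and this may impact the rate in which the primary endpoint occurs".

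**The concern.** Confounding by strategy means that a predictor's association with recurrence is distorted because the predictor also steers the choice of strategy, and strategy affects recurrence. That is a statement about coefficients. The C-statistic is a rank measure whose value depends on how widely risk is spread in the group where it is computed. The characteristics that determine strategy are also likely predictors in the model, so their range is narrower inside a strategy than in the whole cohort. In addition, strategy is constant inside a stratum and adds nothing to ranking there.

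A gap between overall and within-strategy performance therefore mixes at least three things: narrower case mix, the loss of strategy's own contribution to ranking, and confounding. The comparison cannot say which is present. At stake is whether the variables reported as predictors of ablation success partly reflect the treatment that such patients are given. This matters because the article intends the results to guide patient selection and treatment decisions.

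**Working it through.** **The plan's own figures.** The article gives no figure for this check. Its sample-size figures supply the event rate and cohort size, and they reproduce: 5 × 3 + 2 + 1 = 18 variables; 18 × 10 = 180 events; 180 / 0.32 = 562.5, so 563 patients. With 15% loss, 650 × 0.85 = 552.5 patients remain.

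**Two-strategy simulation.** From the article: 32% recurrence, and strategy allocated on prognostic factors. Assumed: everything else. N = 400,000 per scenario.

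- Outcome: logit P(recurrence) = a + b·x + 0.5·z + c·S, with x and z standard normal, b = 0.8, and a set to give 32% events.
- Allocation: P(S = 1) = 1 / (1 + exp(−2.5x)), or 0.5 if random.

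| Scenario | Confounded? | Log OR of x, without S / with S | AUROC, S in model: whole → S=0 / S=1 | AUROC, S not in model: whole → S=0 / S=1 |
|---|---|---|---|---|
| A: by x, c = 0 | no | 0.79 / 0.79 | 0.730 → 0.699 / 0.698 | 0.730 → 0.699 / 0.698 |
| B: by x, c = −1.2 (protective) | yes | 0.39 / 0.80 | 0.701 → 0.698 / 0.701 | 0.663 → 0.688 / 0.691 |
| C: by x, c = +1.2 (harmful) | yes | 1.20 / 0.80 | 0.808 → 0.703 / 0.697 | 0.789 → 0.699 / 0.693 |
| E: random, c = +1.2 | no | 0.74 / 0.79 | 0.761 → 0.732 / 0.728 | 0.717 → 0.732 / 0.728 |

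Reading the table:

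1. With S in the model, A and E show a drop of about 0.03 (0.730 − 0.699 = 0.031; 0.761 − 0.732 = 0.029) and neither is confounded.
2. B is strongly confounded, yet the drop is 0.003 and 0.000. With S left out, the AUROC is higher within strategies (0.688 and 0.691 against 0.663).
3. C is confounded and the gap widens (0.808 − 0.703 = 0.105). Confounding can therefore show in the gap, but its sign depends on the direction of the strategy effect.
4. The change in the log odds ratio tracks confounding: 0.00 in A, 0.80 − 0.39 = 0.41 in B, 0.80 − 1.20 = −0.40 in C. In E it is 0.79 − 0.74 = 0.05 without confounding, because odds ratios are not collapsible. Small changes should not be over-read.

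**Three-strategy simulation at the planned size.** Assumed: groups of 50%, 30% and 20% cut on substrate score plus noise; a second predictor with log odds ratio 0.4; substrate log odds ratio 0.7 with no strategy effect, or 1.1 with strategy effects −0.8 and −1.6. The model is fitted without strategy and n = 552.

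| | No strategy effect | Strong confounding, protective strategies |
|---|---|---|
| Mean AUROC drop (SD) | +0.048 (0.018) | −0.013 (0.014) |
| Mean change in substrate coefficient when strategy is added (SD) | 0.00 (0.13) | +0.54 (0.14) |

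Here the AUROC gap points the wrong way, while the coefficient change separates the two cases.

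**The second performance measure.** A logistic model with strategy as a main effect reproduces each strategy's observed event rate by construction, so mean observed minus predicted is zero in every strategy whether or not strategy confounds. It is informative only from the model without strategy: +4.2, −1.3 and −8.6 percentage points in the strongly confounded case.

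**Precision.** Hanley–McNeil variance: [A(1−A) + (m−1)(A/(2−A) − A²) + (k−1)(2A²/(1+A) − A²)] / (mk), with m events and k non-events. At A = 0.70 and 32% events, n = 150 gives m = 48, k = 102, SE 0.048 and a 95% half-width of 0.09. The half-width is about 0.05 at n = 553, 0.13 at n = 75 and 0.16 at n = 50. The subgroup sizes are assumptions. Shifts of 0.03 would be lost in the smaller strategy groups.

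**The case against.** **Strategy is already in the plan for the model.** This carries weight. Technique is a candidate predictor and interactions with it are tested. In the three-strategy set-up with strong confounding, forward AIC selection at n = 552 (400 cohorts) kept strategy in 98% of cohorts, with a mean substrate coefficient of 1.10 against a true 1.10. At half that strategy effect it was kept in 64%, with a mean of 1.07, against 0.82 if strategy is always omitted. A reader might infer from the simulations that the planned model will be badly biased, with coefficients halved. The article does not support that: such a bias arises only in a model from which strategy has been dropped. What remains is that the article does not say strategy is kept, so individual fits that drop it can be biased.

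**The plan is not the AUROC alone.** Correct: observed outcome by predicted risk is also named, and it would reveal a misfit by strategy if strategy were left out. It is uninformative on average once strategy is in.

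**No decision rule is stated.** Also correct. A reader might infer that a lower subgroup AUROC will be declared confounding and a stable one taken as reassurance. The article sets no threshold and describes the analyses as done "separately for patients treated with different ablation strategies for sensitivity purposes". Detail of interpretation may sit in documents not shown. The purpose, however, is stated, and no reading of the gap alone serves it.

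**The model is exploratory and predictive.** Performance by strategy is worth reporting for that reason, and nothing here argues for removing it.

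**Conclusion.** Wrong as written: the method does not match its stated purpose. The gap between whole-cohort and within-strategy performance cannot separate case mix from confounding. It can show a drop with no confounding, and can stay flat or reverse when a protective strategy goes to higher-risk patients.

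It would go too far to say that the gap is unrelated to confounding, since a harmful strategy effect widens it. It would also go too far to say that strategy is otherwise uncontrolled, given the candidate predictor and interaction terms. The effect on the main model is therefore limited and conditional on strategy being dropped in selection.

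The argument rests on the article's own account that strategy follows prognostic characteristics and that success differs by strategy. The simulated sizes rest on assumed effects, allocation and group sizes, and show direction only.

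**What to change.** 1. Describe the strategy-specific performance analyses as a check of discrimination and heterogeneity across strategies, not of confounding.
2. State that ablation strategy is kept in the model whatever the AIC selection does.
3. Assess confounding by refitting the final model with and without strategy, and report the change in each predictor's log odds ratio with a bootstrap confidence interval. Judge the size of the change, since non-collapsibility alone can produce a small one. Where an interaction with strategy is retained, make the comparison on the main-effects version and show strategy-specific log odds ratios beside it.
4. If observed minus predicted recurrence by strategy is reported, compute it from the model without strategy.

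The cost is revised wording and a little extra analysis. No new data, visits or patients are needed, and the strategy-specific performance results stay in the report under a different label.
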